**Fig. 2 Fig2:**
[figure not shown]
Temporal structure of the intervention (Rehabilitation Program - CORE-Study)

### Adherence

The number of sessions completed and the number of sample losses will be recorded and considered in the analysis and discussion of the results. As strategies to optimise adherence, the present trial presents a wide range of schedules available for carrying out the intervention. In addition, affectivity to exercise will be monitored at some points during the intervention. WhatsApp groups will be created with patients and care/intervention providers to facilitate communication, and telephone contact with management (first moment) or coordination (second moment) will occur when two or more consecutive absences from the intervention occur. In these calls, the focus will be on getting to know the patient’ clinical situation and asking if there is anything that the research team can help with in order to maintain the follow-up in the study.

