### Intervention

The intervention will last 24 weeks and will consist of two weekly training sessions in the first 11 weeks, reassessments in the 12th week and three weekly sessions from the 13th to 24th weeks. The planned training will have two major stages, the first consisting of two mesocycles, with progression primarily in volume, and the second consisting of three mesocycles, with progression primarily in the intensity (Table 1).

**Table 1 Tab1:** Structuring of training sessions throughout the Rehabilitation Program (CORE-Study)

**Weeks**	**Structure (Component-type, volume, intensity, progression)**
1	Familiarisation with the training model (focus on learning movements and perceived effort)
2 a 6	**Balance**—3 exercises performed in three sets of 10–30 s, with evolution in time (10 to 30 s) and complexity (stages). Unipedal balance—standing on one foot, balance transitioning from dorsiflexion to plantar flexion, and getting up from a chair and walking in a straight line. The stages are (1) Support from both hands (chair/instructor/wall); (2) One-handed assistance (chair/instructor/wall); (3) No assistance; (4) With eyes closed. **Aerobic (treadmill walking)**—total: 25 min accumulating 15 min of light intensity (RPE: 12/13) and 9–10 min of passive recovery). Duration of blocks in two levels—5 repetitions of 3-min walk with 2-min passive intervals, or 3 repetitions of 5-min walk with 3-min passive intervals. **Resistance (body weight and rubber band)**—Stretch bench press, Sit and Stand, Neutral Rubber Row, Step Up and Down Step and Plantar Flexion (2 sets of 10 to 15 reps at RPE 12/13, interval of 1 min).

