### Control procedure

Patients allocated to the control group will receive recommendations about physical activity and sedentary behaviour. For this, two chapters from the Brazilian Guide to Physical Activity [20] will be provided and explained to patients during a personal meeting. One chapter is entitled “Understanding Physical Activity”, and the other procedural chapter is entitled “Physical Activity for Adults” or “Physical Activity for the Elderly”, depending on the age group of the participants.

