### Adverse events and intervening factors

From the medical screening, eligibility criteria, monitoring and safety measures described, and the structure of the rehabilitation programme, we believe that the risk for adverse events, especially serious ones, is minimal. Furthermore, physical tests of greater cardiovascular overload will only be performed in a hospital environment or in the presence of a physician, for greater patient safety. However, if any event occurs, the patients will be treated immediately by the team involved in the research.

During the intervention, patients who are in the intervention group will respond every Friday to a recall questionnaire of adverse events of the last 7 days. Patients will answer simple questions about possible events, unusual physical activity, medication changes, diagnoses and medical care, pain related or not to physical activity, and general well-being. Patients in the control group will be contacted via video call every 6 weeks to control adverse events and will answer the same questionnaire applied weekly to the intervention group.

The possibility of discontinuation of the study will be discussed by the three coordinators ([name], [name] and [name]) in the event of a serious adverse event or a succession of mild and moderate adverse events.

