### Analysis plan

Continuous sample characterisation variables will have their normality and homogeneity tested by the Shapiro-Wilk and Levene tests, respectively. Those with normal distribution will be described by mean and standard deviation, and the others will be described by median and interquartile range. The categorical variables of sample characterisation will be described by absolute frequency (*n* sample) and relative (%).

To analyse the effects of the rehabilitation programme, generalised estimation equations will be used, adopting the Bonferroni post hoc. Outcomes will be analysed in two ways (by protocol [PP] and intention to treat [ITT]). For this, patients who complete at least 70% of the proposed sessions will be included in the PP analysis. For ITT analysis, all available data of all patients will be used. For this, all patients will be invited for endpoint evaluations, independently of adherence. For missing data, multiple imputation considering the maximum likelihood estimation approach will be used. Effect sizes (ES) will be calculated using Cohen’s *d* test (Cohen 1988), being considered as small values (0.20 ≤ *d* < 0.50), medium (0.50 ≤ *d* < 0.80) and great (*d* ≥ 0.80).

The significance index adopted will be 0.05. The statistical treatment of the data will be carried out using SPSS (Statistical Package for the Social Sciences), version 22.0.

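### The only retention call described is triggered by missed training sessions, so it cannot reach controls; an arm-neutral trigger would cheaply lower the risk of differential loss at week 24

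*Protocol article*

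**What the plan says.** The Adherence section lists measures to support adherence. One is active: "telephone contact with management (first moment) or coordination (second moment) will occur when two or more consecutive absences from the intervention occur". The call is not only about training. The section says that it includes "asking if there is anything that the research team can help with in order to maintain the follow-up in the study".

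The Intervention section sets the session frequency: "two weekly training sessions in the first 11 weeks, reassessments in the 12th week and three weekly sessions from the 13th to 24th weeks". The Control procedure section gives controls guide chapters that "will be provided and explained to patients during a personal meeting"; it schedules no sessions.

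The section on adverse events sets the routine contact in each arm. In the training arm, "patients who are in the intervention group will respond every Friday to a recall questionnaire of adverse events of the last 7 days". In the other, "Patients in the control group will be contacted via video call every 6 weeks to control adverse events".

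Three provisions do not depend on arm, or are not restricted by it:
- The Analysis plan says that "all patients will be invited for endpoint evaluations, independently of adherence". It also plans generalised estimating equations, an intention-to-treat analysis on all available data, and imputation of missing data.
- The Functional capacity section measures 6MWD at baseline, week 12 and after 24 weeks, without limiting this to one arm.
- The Adherence section says that "WhatsApp groups will be created with patients and care/intervention providers to facilitate communication", without saying which arm's patients.

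The Sample size calculation section plans one loss figure, about 30%, for both groups.

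**The concern.** A step meant partly to keep people in the study is tied to an event that can happen in only one arm. A training patient who begins to drift misses two sessions and is called by management, then by coordination. A control who begins to drift has no session to miss, and the contact described for that arm is less frequent and has a different purpose.

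Patients know their allocation, since the Randomisation section has them told individually; only the outcome assessors are blinded. With 30 patients per group and about 30% expected loss, each group keeps only about 21 or 22 patients for the week-24 comparison. If unequal retention effort led to unequal loss, and if those lost differed in 6MWD from those kept, the patients compared at week 24 would no longer be the groups that were randomised. Imputation that assumes loss is explained by observed data would not correct the part that depends on the unobserved outcome.

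**Working it through.** **1. The plan's own loss allowance.** Inputs from Sample size calculation: 22 per group, about 30% loss, target 30 per group.
- 22 / (1 − 0.30) = 31.4, so 32.
- 22 × 1.30 = 28.6, so 29.
- Going from 30 to 22 is a loss of 8/30 = 26.7%.

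The stated 30 lies within two patients of either method and fits a loss of around 30%. It is one figure for both groups; no loss rate by arm is given.

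**2. Contact interval.** Time to two consecutive absences = 2 / sessions per week.
- Weeks 1 to 11: 2/2 = 1 week.
- Weeks 13 to 24: 2/3 = about 0.7 week.
- Controls: one call every 6 weeks. Ratios: 6/1 = 6 and 6/(2/3) = 9.

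**3. What can trigger the retention call.**

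| | Training arm | Control arm |
|---|---|---|
| Sessions that can be missed | 2 to 3 per week | none |
| Routine adverse-event contact | weekly questionnaire | video call every 6 weeks |
| Stated trigger for a retention call | two or more consecutive absences | none stated |
| Invitation to endpoint evaluation | yes | yes |
| Week-12 6MWD | yes | yes (not restricted by arm) |

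The first and third rows are the point. The last two rows are safeguards common to both arms.

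**4. Size of a possible bias (illustration; loss rates and gap are assumed).** Let D be the number of metres by which the mean 6MWD of stayers exceeds that of leavers, taken as equal in both arms. In an arm with loss l, the complete-case mean exceeds the full-arm mean by l × D. For training minus control:

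bias = (loss in training − loss in control) × D

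| Loss, training / control | D = 0 | D = 30 m | D = 50 m |
|---|---|---|---|
| 30% / 30% | 0 | 0 | 0 |
| 20% / 40% | 0 | −0.20 × 30 = −6 m | −0.20 × 50 = −10 m |
| 40% / 20% | 0 | +0.20 × 30 = +6 m | +0.20 × 50 = +10 m |

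If leavers walk further than stayers, D is negative and every sign reverses. Against the 50 m difference used for the sample size, 6 to 10 m is 12% to 20%.

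These are complete-case figures on raw means. The planned analysis also uses baseline and week-12 6MWD, so any part of the gap already visible there can be taken into account, and only the unexplained part would remain as bias.

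**5. Power is hardly affected.** No standard deviation is given. The value that makes 22 per group give 80% power for 50 m (two-sided 0.05, normal approximation) is 50 / (√(2/22) × (1.960 + 0.842)) = about 59 m. With that value, 21 and 21 completers give 78% power; 24 and 18 give 77%. The issue is possible bias, not lost precision.

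**The case against.** The strongest reply is that this is an adherence measure in an adherence section. A call after missed sessions has no natural counterpart in an arm without sessions, and a journal article commonly leaves to the full protocol how staff chase a missed call or visit. That stands as far as silence goes. It does not cover the rule that is stated: a call aimed partly at continued follow-up has a trigger that controls can never meet.

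A reader might infer more than the document supports:
- *That loss at week 24 is likely to differ by arm and bias the primary comparison.* No loss rate by arm is given. The training arm carries two to three on-site sessions a week and could lose more patients, in which case the call might narrow an imbalance.
- *That a control's missed call or visit triggers nothing, or that controls get a single invitation at week 24.* The article says neither. It does not describe such a step, and it does not say how many invitations are sent. It also names a manager responsible for contact with patients (Randomisation) and managers who schedule the evaluations (Coordination and management of the trial).
- *That controls are out of touch for months.* The 6-weekly calls and the week-12 assessment make this less plausible, and the messaging groups may include controls.

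The invitation regardless of adherence already separates assessment from training to a good extent, and the longitudinal analysis with imputation reduces the risk further. Neither removes it. An invitation is not tracing, the week-12 value helps only if that visit took place, and imputation from observed data does not correct loss that depends on the unseen outcome.

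**Conclusion.** The point holds as a cheap improvement, not as a demonstrated bias. Retention effort, as described, is unequal by arm, and this creates an avoidable risk of differential loss for the week-24 6MWD. Whether loss will differ, by how much and in which direction cannot be derived from the document.

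As a scale, the illustration gives at most about 6 to 10 m either way. It rests on an assumed 20-point difference in loss, an assumed gap of 30 to 50 m between leavers and stayers that is the same in both arms, and a complete-case comparison. The bias is zero if loss is unrelated to 6MWD, or if loss and gap are equal in the two arms.

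**What to change.** Make the trigger in the Adherence section arm-neutral. In either arm, missed scheduled contacts (sessions for training, the 6-weekly call for controls) or a missed week-12 assessment should prompt the same two calls, by management and then coordination, with the same script. The script should ask the patient to attend the remaining assessments whatever their training status, and keep that request apart from any encouragement to train. Report loss and its reasons by arm; the section already provides for recording losses.

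The cost is a few more calls by existing managers and slightly more contact with controls, with no new visits or staff.

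Its reach is limited. The Trial status section puts the last block's recruitment in October 2022 and protocol version 1.0 at 1 December 2022. With 2 + 24 + 2 = 28 weeks per patient, a block starting in October 2022 would finish between about mid-April and mid-May 2023. At the version date the change could therefore help only controls still in follow-up. Reporting loss by arm applies to everyone.

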### Control procedure

Patients allocated to the control group will receive recommendations about physical activity and sedentary behaviour. For this, two chapters from the Brazilian Guide to Physical Activity [20] will be provided and explained to patients during a personal meeting. One chapter is entitled “Understanding Physical Activity”, and the other procedural chapter is entitled “Physical Activity for Adults” or “Physical Activity for the Elderly”, depending on the age group of the participants.

### Outcomes

The evaluation of all outcomes will be blinded and performed by experienced researchers. In addition to being evaluated at baseline, the outcomes of functional capacity, anthropometrical and body composition, cardiovascular and psychosocial parameters will be reassessed at the 12th and after 24 weeks of the rehabilitation programme. Other parameters derived from the neuromuscular, respiratory, cardiorespiratory and behavioural assessments will only be carried out at baseline and at the end of the intervention period (after 24 weeks), due to logistical reasons.

### Primary outcomes

The primary outcome was the functional indicator of cardiorespiratory fitness after 24 weeks assessed by the 6-min walking test (6MWT), following the protocol of the American Thoracic Society [21] and recorded as 6MWD in meters.

### Secondary outcomes

As secondary outcomes, indicators of functional capacity, neuromuscular parameters, anthropometrical and body composition, respiratory, cardiovascular, cardiorespiratory, behavioural and psychosocial parameters will be evaluated.

### Characterisation variables

Patients included in the study will respond to an anamnesis containing sociodemographic information (sex, age), clinical history related to the period of COVID-19 infection (need and duration of ICU hospitalisation, complications acquired in the hospital environment, need for oxygen and ventilation) and general health (comorbidities, medication use, history of injuries and/or surgeries). In addition, information regarding the patient’ exercise background will be collected.

### Safety and training monitoring

As monitoring and safety variables, information on external and internal training load, SpO_2_, heart rate, blood pressure, capillary blood glucose and affective response to exercise will be collected. The internal load of each training session will be quantified by the session RPE method (RPE session), using the adapted Borg CR1 scale [22] in order to estimate the intensity after each exercise session. For such measurement, it will be asked, individually, how was the perceived intensity of the training session. In addition to RPE, heart rate (HR) will be recorded during and after the aerobic section of training, being another parameter of internal load and important for hemodynamic safety.

The quantification of the external load will be performed by recording a representative parameter of volume in the aerobic and resistance training components. In aerobic training, the volume will be represented by the distance covered on the treadmill. In the resistance component, the volume will be represented by the number of repetitions (average between sets and/or total) in the sitting and standing exercise in phase 1 and in the leg press in phase 2. These load quantifications will be performed in all sessions of the intervention.

The SpO_2_ will be assessed by finger oximetry, during and after all exercise sessions, by pulse oximeter (HC261 Multilaser) throughout phase 1 and at least before sessions in phase 2 of the rehabilitation programme.

For safety, blood pressure will also be measured before all mesocycle 1 exercise sessions and will continue to be measured before all sessions in patients who have hypertension or some hemodynamic alteration. The evaluation will be performed using automatic equipment (OMRON, model HEM-7113, Brazil), following the procedures described by Barroso [23]. For safety, patients who have blood pressure values [3] 160 mmHg for systolic blood pressure and/or [3] 105 mmHg for diastolic blood pressure will not be able to start the exercise session. Additionally, to analyse the acute effect of exercise, blood pressure values will be measured immediately, 15 and 30 min after the first and last session of each training mesocycle.

Capillary blood glucose collections will be performed, primarily for safety, only in patients with glycaemic alterations. The number of assessment sessions will be defined individually. For exercise purposes, glycaemic values will be measured before, immediately, 15 and 30 min after the first and last session of each training mesocycle. These collections will be performed by means of a digital puncture with disposable lancets (*Accu-Check Safe-T-Pro Uno,* Roche, Portugal) and a drop of capillary blood will be used to fill a test strip that will be analysed in a clinical glucometer (*Accu-Check Performa,* Roche, Portugal) that assesses the blood glucose concentration at the time of collection in approximately 5s.

The affective response to the exercise will be determined from the sensation scale of Hardy and Rejeski [24]. This instrument is composed of an 11-point scale, ranging from +5 (“very good”) to −5 (“very bad”). To use this instrument, at the end of the first and last session of each mesocycle, participants will answer the following question: “How pleasant was it for you to perform this exercise session?”

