7 a 11	**Balance**—3 exercises performed in three sets of 10–30 s, with evolution of time (10 to 30 s) and complexity (stages). Unipedal balance—standing on one foot, balance transitioning from dorsiflexion to plantar flexion, and getting up from a chair and walking in a straight line. The stages are (1) Support from both hands (chair/instructor/wall); (2) One-handed assistance (chair/instructor/wall); (3) No assistance; (4) With eyes closed. **Aerobic (Treadmill walking)**—total: 25 min (20 min at light intensity (RPE: 12/13) interspersed with 5 min of passive recovery). Duration of blocks in two levels—5 blocks of 4 min of walking with passive 2-min intervals, or 4 blocks of 5-min walking with 2-min passive intervals. **Resistance (body weight and rubber band)**—Stretch bench press, Sit and Lift, Neutral Rubber Row, Step Up and Down Step and Plantar Flexion (3 sets of 10 to 15 reps at RPE 12/13, interval 1 min)—same setting from above.
12	Reassessments of the outcomes from Functional Capacity, Anthropometry and Body Composition, Cardiovascular Parameters and Psychosocial Parameters.
13 a 16	**Aerobic (Walking—treadmill or athletic track*)**—Continuous training—25 min at moderate intensity (RPE: 12/13). **Resistance (machines and free weights)**—Horizontal Leg Press, Sitting Row, Flexion Chair Knee Flexion, Vertical Peck Deck, Plantar Flexion with Back Barbell (3 sets of 12 to 15 RM, 1 min interval)
17 a 20	**Aerobic** (Walking - treadmill or athletic track*)—Interval training—5 repetitions of 5 min (1 min at RPE 15 with 4 min at RPE 12/13). **Resistance (machines and free weights)—**Horizontal Leg Press, Seated Row, Flexion Chair Knee Flexion, Vertical Peck Deck, Plantar Flexion with Barbell on the Back (3 sets of 10 to 12 RM, 1 min interval).
21 a 24	**Aerobic (Walking—treadmill or athletic track*)—**Interval training—6 repetitions of 4 min (1 min at RPE 15 with 3 min at RPE 12/13). **Resistance (machines and free weights)—**Horizontal Leg Press, Seated Row, Flexion Chair Knee Flexion, Vertical Peck Deck, Plantar Flexion with Back Barbell (3 sets of 8 to 10 RM, 1 min interval)

*RPE* rate of perceived effort, *reps* repetitions, *MR* maximum repetitions

*Dependent on climatic factors and the clinical condition of the patients

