### Functional capacity

The assessments of functional capacity will be performed at baseline, at week 12 and after 24 weeks of intervention. The functional indicator of cardiorespiratory fitness and the primary outcome of the study will be evaluated by the 6-min walk test, following the protocol of the American Thoracic Society [13], which consists of measuring the total walking distance in a predetermined area of 30 m long during 6 min. During the test, the patient will be encouraged by the evaluator through standardised incentive phrases, every minute respectively: “There are 5 min left to finish the test. Keep the pace”; “There are 4 min left to finish the test. Keep the pace”; “You’ve already taken half the test. Keep the pace”; “One min. to finish the test. Keep the pace”; and finally, when the timer reaches zero or reaches 6 min, “Stop”. Every 2 min, during the patient’s walking, the values of the distance covered, HR, SpO_2_, dyspnea effort and RPE will be recorded. The test will be stopped immediately if the patient reports chest pain, intolerable dyspnea, leg cramps, staggering gait, diaphoresis and a pale or grey appearance, or if there is a decrease in SpO_2_ of more than 4%. If the test is stopped for any of these reasons, the patient should be seated or lie supine. After the test is properly completed, the number of laps completed will be recorded as well as the total distance covered, blood pressure (systolic and diastolic), O_2_ saturation, heart rate, dyspnea effort (Borg Scale CR-10) and lower limbs (LL) effort (Borg Scale CR-10). The referred physiological and effort measures will be evaluated also in the first, second, third and sixth minute of recovery. After 15 to 20 min of recovery, the test is performed again, following the same protocol, adopting the better score as the final outcome.

Functional mobility (dynamic balance and agility) will be evaluated by the Timed-Up-and-Go (TUG) test. The TUG will follow the following protocol: from a sitting position in a chair (with back supported), the subjects will get up from it (without the help of hands), walk and go around a Chinese demarcation plate positioned on the ground 3 m away and will sit again (with their backs supported). Two attempts will be made at each of the speeds: maximum (TUG-m) and usual (TUG-h), with a 1-min interval between each attempt, with the shortest time for each speed being recorded [25].

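### In phase 2 only a pre-session SpO2 reading is required, so saturation under effort need not be measured in any of its 36 sessions, including the 24 with RPE 15 bouts

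*Protocol article*

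**What the plan says.** The Safety and training monitoring section lists SpO2 among the monitoring and safety variables and sets its schedule by phase: "during and after all exercise sessions, by pulse oximeter (HC261 Multilaser) throughout phase 1 and at least before sessions in phase 2". In the same section, "heart rate (HR) will be recorded during and after the aerobic section of training", with no restriction to one phase, and session RPE is collected after every session.

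The Intervention section gives two sessions a week in weeks 1 to 11, reassessment in week 12, and "three weekly sessions from the 13th to 24th weeks". The second stage is described as progressing mainly in intensity. Table 1 sets the aerobic work as follows:

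- Weeks 2 to 11: walking blocks at RPE 12/13 with passive rests.
- Weeks 13 to 16: "Continuous training—25 min at moderate intensity (RPE: 12/13").
- Weeks 17 to 20: "5 repetitions of 5 min (1 min at RPE 15 with 4 min at RPE 12/13").
- Weeks 21 to 24: "6 repetitions of 4 min (1 min at RPE 15 with 3 min at RPE 12/13").

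Resistance work changes in week 13 from body weight and rubber bands to machines and free weights at 12 to 15 RM, and reaches 8 to 10 RM in weeks 21 to 24.

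Outside training, SpO2 is recorded during the 6-minute walk test. The Functional capacity section states: "The assessments of functional capacity will be performed at baseline, at week 12 and after 24 weeks of intervention". Among the reasons for stopping that test it lists "or if there is a decrease in SpO_2_ of more than 4" per cent.

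**The concern.** The required oximetry becomes weaker at the point where the training becomes harder. Phase 1, prescribed at RPE 12/13, must have readings during and after each session. Phase 2, which brings heavier resistance work and then RPE 15 bouts, need only have a reading beforehand.

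The protocol itself treats a fall of more than 4% under effort as a reason to stop the walk test. At the phase-2 minimum, the same fall in a training session would go unmeasured. Entry requires SpO2 above 90%, so a patient may start with little margin.

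Two things are at stake. One is the chance to notice desaturation that causes no symptoms. The other is the basis for any later statement about saturation in phase 2, since the Discussion expects the trial to provide safety data and optional readings would not form a consistent record.

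**Working it through.** **Matching the terms.** The Intervention section speaks of stages and the safety section of phases. The safety section takes resistance volume from sit-to-stand in phase 1 and from the leg press in phase 2. In Table 1 the leg press appears only from week 13, so phase 2 is stage 2, weeks 13 to 24.

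**Session counts.** The article gives no session total to reproduce. From the weekly frequencies:

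| Period | Calculation | Sessions | Exertional SpO2 required |
|---|---|---|---|
| Phase 1, weeks 1–11 | 11 × 2 | 22 | yes |
| Weeks 13–16 | 4 × 3 | 12 | no |
| Weeks 17–20 (RPE 15) | 4 × 3 | 12 | no |
| Weeks 21–24 (RPE 15) | 4 × 3 | 12 | no |

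- Phase 2: 12 + 12 + 12 = 36 sessions, and 36 / (22 + 36) = 36/58 = 62% of the programme.
- RPE 15 sessions: 12 + 12 = 24, and 24/36 = 67% of phase 2.
- One-minute RPE 15 bouts per patient with full attendance: 12 × 5 + 12 × 6 = 132.

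**Where exertional SpO2 is next seen.** The week-12 walk test precedes the first RPE 15 session by the 12 sessions of weeks 13 to 16. The next stated exertional reading is the walk test after week 24. The maximal cycle test is done only at baseline and after week 24, and SpO2 is not among its stated measurements.

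**Size of the proposed change.** RPE 15 sessions (24) plus the first and last session of weeks 13 to 16 (2) make 26 of 36, or 72%. The first and last sessions of the other two mesocycles are already among the 24.

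**Patients the change could still reach.** The Trial status section gives recruitment from November 2021 to October 2022, two weeks of evaluation and then 24 weeks of intervention. Week 17 therefore starts 2 + 16 = 18 weeks after recruitment, and week 24 ends 2 + 24 = 26 weeks after it. Assumptions: training starts two weeks after recruitment, recruitment is even over 1 November 2021 to 31 October 2022 (365 days), and 30 patients are trained.

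| Reference date | At least one phase-2 session left | All 24 RPE 15 sessions ahead |
|---|---|---|
| 1 December 2022 (version date) | recruited after 2 June 2022: 151/365 × 30 = 12.4 | recruited from 28 July 2022: 95/365 × 30 = 7.8 |
| 19 January 2023 (publication) | recruited after 21 July 2022: 102/365 × 30 = 8.4 | recruited from 15 September 2022: 46/365 × 30 = 3.8 |

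**The case against.** The best defence is that this is a deliberate, risk-based step-down. Blood pressure is handled in the same way: all patients in the first mesocycle, then only those with hypertension or a haemodynamic alteration. By week 13 each patient has had up to 22 sessions with exertional oximetry and a week-12 walk test, done twice per visit, with a stopping rule for desaturation. Patients were screened clinically and by ECG, had stable respiratory symptoms and no severe dyspnoea, and had cycled to exhaustion at baseline. Heart rate, session RPE, supervision and weekly adverse-event recall continue. The phase-2 rule is a minimum, so staff may go on measuring a patient who gives concern. Nothing in the article gives a rate for new desaturation after all this.

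Most of that stands, and it narrows the concern. It does not remove it, because none of these safeguards measures saturation at the higher phase-2 load, and a permitted reading is not an assured one.

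A reader might infer more than the text supports:

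- **That oximetry stops in phase 2, or that patients are unmonitored.** A pre-session reading is required, further readings are allowed, and other monitoring continues.
- **That patients were harmed, or that desaturation is likely.** The article shows only that it could go unseen.
- **That weeks 13 to 16 are no harder than phase 1.** RPE 12/13 is kept for the aerobic part only; resistance work moves to machines and free weights at 12 to 15 RM.
- **That a change would give about 12 of 30 patients full cover.** That figure includes anyone with a single phase-2 session left. The number with every RPE 15 session still ahead is about 8 at the version date and about 4 at publication.

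**Conclusion.** The point holds in limited form. As written, exertional SpO2 need not be measured in any of the 36 phase-2 sessions, including the 24 in weeks 17 to 24 with RPE 15 bouts. This follows directly from the stated schedule and rests on no assumption beyond equating phase 2 with stage 2.

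The residual risk is new desaturation without symptoms at a load above that of phase 1. Its frequency cannot be estimated from the article. The matter concerns patient safety and the basis of safety reporting; the primary analysis of 6-minute walk distance is unaffected. It is worth changing because the remedy is cheap, but it does not undermine the trial. The counts of patients still reachable depend on the recruitment, start-date and group-size assumptions given with the calculation.

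**What to change.** **Sessions not yet done.** Require SpO2 before, during and after the aerobic section, with the existing oximeter, in all RPE 15 sessions and at the first and last session of each phase-2 mesocycle. Blood pressure and affect readings, and glucose in patients with glycaemic alterations, are already scheduled at those first and last sessions, and heart rate is already recorded during and after the aerobic section. State an action threshold. Its value is for the investigators to set; the walk-test limit of a fall of more than 4% is one already in the protocol.

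**Sessions already completed.** Report how many phase-2 sessions had a reading during or after exercise, and limit any statement on phase-2 desaturation to those sessions.

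**Cost.** A brief finger reading in up to 26 sessions per patient. Some stage-2 aerobic sessions may take place on the athletics track, so the oximeter may have to be carried there. Monitoring would differ between earlier and later recruitment blocks, so the readings should be reported by block.
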